### Participant timeline {13}

The schedule of patient enrolment, interventions, and assessments is reported in Fig. 1.

**Fig. 1 Fig1:**
[figure not shown]
Schedule of enrolment, interventions, and assessments

The study flow chart is reported in Fig. 2

**Fig. 2 Fig2:**
[figure not shown]
Study flow chart

### Sample size {14}

The study is powered to assess the primary endpoint, which is time to negative conversion of nasal swabs for SARS-CoV-2. Based on the recent paper by Hung [11] and assuming a median time to negative conversion of nasal swabs for SARS-CoV-2 of 12 days in the standard of care group and 7 days in the IFNβ-1a group, to detect an HR of 0.58, with a power of 80% at 5% significance level, with an accrual duration of 6 months and a follow-up of 29 days, 120 total patients need to be randomized in 2:1 ratio. With a drop out of 5%, 126 patients will be accrued: 84 patients in the IFNβ-1a arm and 42 in the standard of care arm.

### Recruitment {15}

As stated above, San Raffaele Hospital is the largest clinical Hospital within the Gruppo San Donato (GSD) hospital network located in the Lombardy region, with a total capacity of more than 5000 beds. During the recent COVID-19 outbreak between February 23 and the end of May 2020, more than 1000 people diagnosed with COVID-19 were hospitalized at the San Raffaele Hospital and another 4000 in the remaining hospitals of the GSD network. Moreover, the San Raffaele Hospital has recently been identified as one of the reference hubs in the Lombardy Region. Therefore, in case of a second outbreak of COVID-19, the San Raffaele Hospital and the connected GSD network will easily have access to the diseased population and to patients suitable to trial recruitment.

### Assignment of interventions: allocation

#### Sequence generation {16a}

Patients will be randomized 2:1 to IFNβ-1a (active treatment) or standard of care (control arm), using a computer-generated list of random treatment allocations produced prior to the study start. The permuted block randomization method will be used. The block size will not be disclosed, to ensure concealment.

#### Concealment mechanism {16b}

Sequentially numbered, opaque, sealed envelopes will be used. Envelopes must be opened sequentially. To prevent subversion of the allocation sequence, the name and date of birth of the participant will be written on the envelope before opening it.

#### Implementation {16c}

The statistician will prepare the computer-generated list of random treatment and the staff of the Clinical Trial Center will provide sealed envelopes prior to the study start. The treating physician, who will open the sequentially numbered envelope, will randomize participants who meet all eligibility criteria on visit 2. For every randomization number, the corresponding code for the treatment group of the randomization list will be found inside the envelopes.

### Assignment of interventions: blinding

#### Who will be blinded {17a}

Trial participants, care providers, and data analysts will not be blinded.

#### Procedure for unblinding if needed {17b}

Not applicable, as there is no blinding.

### Data collection and management

#### Plans for assessment and collection of outcomes {18a}

Data will be collected and written in a case report form, (hereafter CRF) in paper format, by the data manager of the study, then will be stored in the principal investigator’s office, stored into the trial master file, including the source documentation reporting the patient’s data inserted in CRF, ready to be monitored by the CRA of the study. The source documentation reporting sensitive data, after the monitoring activity, will be anonymized, using the predefined study code for each patient.

#### Plans to promote participant retention and complete follow-up {18b}

There will be no specific plan for promoting participant retention and complete follow-up. Patients who discontinue or deviate will be followed up in the Outpatient Clinic and monitored for survival.

#### Data management {19}

After the monitoring activity, the data will be inserted in an Excel file, with restricted access (required password) stored on the institutional computer of the data manager (access requiring password, and automatic back-up in the main server), placed in his study, and, when planned in the protocol, the data will be transferred to the statistician, using an electronic support (flash drive), for the statistical analysis.

#### Confidentiality {27}

In accordance with European Regulation (EU) 2016/679 and current Italian Data Protection of Personal Authority, the collection and storage of personal health data will be limited to study-related information and will not be disclosed, made available, or otherwise used. All laboratory specimens, reports, data collection, process, and administrative forms will be identified by a coded ID number to maintain participant confidentiality. Only the physician and authorized personnel may be able to link this code to the name. All the information will be stored in locked file cabinets in areas with limited access. All local databases will be secured with password-protected access systems. Participant study information will not be released outside of the study without the written permission of the participant, except as necessary for monitoring by Ethics Committee, Italian and Foreign Regulatory Authorities.

#### Plans for collection, laboratory evaluation, and storage of biological specimens for genetic or molecular analysis in this trial/future use {33}

The collection and storage of biological material in the Biobank of the IRCCS Ospedale San Raffaele will be allowed only if participants accept the informed consent of COVID-BioB. Future research projects will always be submitted for approval to the Ethics Committee of IRCCS Ospedale San Raffaele.

### Statistical methods

#### Statistical methods for primary and secondary outcomes {20a}

Prior to the analysis of the final study data, a detailed statistical analysis plan (SAP) will be written describing all analyses that will be performed. Continuous variables will be described by mean, standard deviation, median, minimum, and maximum. Categorical variables will be described by number and percentage of subjects in each category. The primary efficacy analysis will be done on an intent to treat basis (ITT) and will include all randomized patients. Survival analysis will be performed to address the primary outcome of the study. Time to event is defined as the time from randomization until date of negative conversion. The date of the event (time of negative conversion) is the date of the first negative nasal swab test, confirmed by a second test performed at least 48 h apart. Data for dead patients are censored at the time of the last nasal swab. Survival curves will be estimated using the Kaplan-Meier method and the Log-rank test will be used to compare the outcomes of the different treatment arms. Hazard ratios will be estimated using the Cox proportional hazards model and these will be presented together with 95% two-sided confidence intervals. Endpoints that are measured as time from randomization will be compared between treatment groups using the Log-rank test. Student’s *t* test or Mann-Whitney test (depending on the data distribution pattern) will be used for inter-group comparison of continuous variables; chi-square test or Fisher exact test will be used for inter-group comparison of categorical variables. The primary analysis set for safety analyses is defined as the safety analysis set, which will include all participants who are randomized and have received at least 1 dose of study treatment. All safety data collected from the randomization date through the last follow-up visit will be summarized by treatment group. Statistical significance will be determined at 5% significance level. Analysis will be performed by SAS software Version 9.2 or later (SAS Institute, Inc., Cary, North Carolina, USA).

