### Eligibility criteria {10}

Participants will be patients aged 18 years or greater, diagnosed with COVID-19 (positive swab RT-PCR detection of SARS-CoV-2 and pneumonia diagnosed with computed tomography (CT)), and with a clinical status of 3, 4, or 5 on a 7-point ordinal scale, consisting of the following: (1) not hospitalized, with resumption of normal activities; (2) not hospitalized, but unable to resume normal activities; (3) hospitalized, not requiring supplemental oxygen; (4) hospitalized, requiring supplemental oxygen; (5) hospitalized, requiring high-flow oxygen therapy, non-invasive mechanical ventilation, or both; (6) hospitalized, requiring extracorporeal membrane oxygenation (ECMO), invasive mechanical ventilation, or both; and (7) death. Exclusion criteria include clinical status defined as category 1, 2, or 6 on the aforementioned 7-point ordinal scale, known allergy or hypersensitivity to IFNβ-1a or IFNβ-1b; presence of severe concomitant illnesses and/or medical conditions that in the physician opinion will not allow participation to the study; pregnant or lactating females; history of major depression disorder or suicidal attempt or suicidal ideation; and spontaneous blood ALT or AST levels > 5 times the upper limit of normal. Starting from the signature of the informed consent, the patient will be considered enrolled in the clinical trial and subject to randomization. Interventions will be performed by the San Raffaele Hospital physicians assigned to the COVID-19 units.

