### Outcomes {12}

#### Primary outcome

Time to negative conversion of SARS-CoV-2 nasopharyngeal swabs. Viral load will be measured by RT-PCR. [Time frame: baseline, days 3, 5, 7, 9, 11, 13, 15, 21, and 29]. IFNβ-1a has direct in vitro antiviral activity against SARS-CoV-2 [9], while IFNβ-1b has been identified as the key therapeutic reducing the time to negative conversion of SARS-CoV-2 nasopharyngeal swabs in a recent trial [11].

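### The primary log-rank test makes no use of baseline viral load or entry clinical status, both collected; pre-specified adjustment would gain power by an amount that depends on how prognostic they are

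*Protocol article*

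**What the plan says.** All references are to the protocol article.

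- **Primary analysis**, Statistical methods {20a}: "the Log-rank test will be used to compare the outcomes of the different treatment arms". For the estimate, "Hazard ratios will be estimated using the Cox proportional hazards model". No strata are named for the test and no covariates for the model. The same section says that "a detailed statistical analysis plan (SAP) will be written describing all analyses that will be performed".
- **Randomisation**, Sequence generation {16a}: "The permuted block randomization method will be used". Allocation is 2:1 from one list, with no stratification factor named.
- **Baseline viral load**, Primary outcome: "Viral load will be measured by RT-PCR. [Time frame: baseline, days 3, 5, 7, 9, 11, 13, 15, 21, and 29". The outcome is defined on nasopharyngeal swabs, so the starting value is on the schedule.
- **Entry status**, Eligibility criteria {10}: patients enter "with a clinical status of 3, 4, or 5 on a 7-point ordinal scale", so the category is known for everyone randomised.
- **Size**, Sample size {14}: the assumed medians are "12 days in the standard of care group and 7 days in the IFNβ-1a group, to detect an HR of 0.58". Power is set to 80% and the test level to 5%; the result is 120 patients, raised to 126 (84 and 42) for 5% dropout.
- **Missing data** {20c}: gaps are not filled, and analysis uses observed cases.

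**The concern.** The outcome is the time until a measured viral quantity is no longer detected, so baseline load is the starting point of the outcome process and a natural candidate for a prognostic factor. Entry status spans patients without oxygen to patients on non-invasive ventilation. As described, neither the allocation nor the primary test takes account of either variable.

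In a proportional-hazards setting, leaving out a prognostic covariate pulls the estimated hazard ratio toward 1 and costs power, even under perfect randomisation. Only the primary endpoint is powered, the control arm has 42 patients, and the design has no margin above 80%. Unstratified allocation also allows a chance difference in starting viral load, which the stated analysis would leave in the estimate.

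**Working it through.** **1. The plan's own figure.** Inputs from Sample size {14}: HR 0.58, two-sided 5%, 80% power, 2:1 allocation.

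Schoenfeld events = (1.960 + 0.842)² / [(1/3)(2/3)(ln 0.58)²] = 119.03, rounded up to 120.

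With exponential medians of 12 and 7 days, 6 months of uniform accrual and at least 29 days of follow-up, 98.2% of controls and 99.7% of IFNβ-1a patients convert, or 99.2% overall. N = 119.03 / 0.992 = 120.0, with 80.0% power. Then 120 × 1.05 = 126 = 84 + 42. The stated size reproduces.

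**2. The same design with each patient observed for 29 days.**

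- Control: 1 − exp(−ln 2 × 29/12) = 0.813.
- IFNβ-1a: 1 − exp(−ln 2 × 29/7) = 0.943.
- Overall: (0.813 + 2 × 0.943)/3 = 0.900, or 108 events from 120 patients.

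Power is 76% by Schoenfeld and 73% to 75% by simulation. This shortfall exists before any covariate is considered.

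**3. Gain from adjustment.** Prognostic strength is not in the article, so it is an assumption and a range is shown. Simulation: 40 against 80 patients, exponential times, control median 12 days, 29-day cap, one standard-normal baseline index, two-sided 5% Wald test, 3000 trials per row. Cells show unadjusted → adjusted power. In the middle column the HR at a given baseline value is fixed at 7/12. In the right column the overall (marginal) HR is held at about 0.58.

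| HR per SD of index | Conditional HR 7/12 | Marginal HR about 0.58 |
|---|---|---|
| 1.00 | 73.0% → 72.8% (−0.2) | 74.9% → 74.7% (−0.2) |
| 1.22 | 68.7% → 70.5% (+1.8) | 72.1% → 73.7% (+1.6) |
| 1.35 | 68.4% → 73.6% (+5.2) | 73.9% → 78.1% (+4.2) |
| 1.49 | 60.9% → 67.5% (+6.6) | 70.2% → 77.1% (+6.9) |
| 1.65 | 59.0% → 71.9% (+12.9) | 70.5% → 81.1% (+10.6) |
| 1.82 | 55.1% → 70.2% (+15.1) | 71.8% → 86.4% (+14.6) |
| 2.01 | 49.8% → 69.4% (+19.6) | 68.5% → 86.9% (+18.4) |
| 2.72 | 37.9% → 67.3% (+29.4) | 72.5% → 95.6% (+23.1) |

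A separate simulation rounded conversions up to the scheduled swab days, counted events to day 21 and used Efron ties (2000 trials per setting, marginal HR 12/7 for conversion, the inverse of the plan's ratio). At log-HR per SD of 0, 0.35, 0.5 and 0.7 it gave 71.1% → 70.9%, 72.4% → 77.5%, 69.0% → 80.0% and 69.9% → 86.1%. The pattern is the same.

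As a cross-check, inflating 108 events by 1/(1 − R²) gives gains of 2, 4, 9, 13 and 17 points at R² of 0.05, 0.10, 0.20, 0.30 and 0.40.

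**4. Chance imbalance.** The standardised baseline difference has SE √(1/84 + 1/42) = 0.19. A difference above 0.25 SD in either direction has probability of about 19% for any one covariate (0.25/0.189 = 1.32).

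**The case against.** The strongest reply is that nothing stated is wrong. An unstratified log-rank test holds its type I error under randomisation, chance imbalance is already part of that error rate, and the test matches the formula that sized the trial. Choosing an adjusted model instead is a choice between two valid methods; it needs a functional form for viral load and changes the hazard ratio to a conditional one. All of this stands, and it limits the point to efficiency and to the precision of the realised estimate.

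A second reply is that Cox covariates, ties and missing-covariate rules belong in the analysis plan still to be written. That stands for the Cox model: a reader might infer that it is unadjusted by design, but covariates are unstated, not excluded. It does not cover the primary test, which the article does name. Timing matters too. The plan need only precede the final analysis, while the trial is open-label and the analysts are unblinded ({17a}), so covariates chosen late could be suspected of following the data.

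A reader might also infer that a fixed amount of power, such as 5 to 16 points, is being lost. No figure in the article supports that. Such a range corresponds to an assumed moderate prognostic strength, and the gain runs from about 0 to more than 20 points over the values tried. Nor was entry status simulated separately; its added benefit is unquantified.

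**Conclusion.** The point holds as a missed efficiency gain in the one powered comparison. It is not an invalid test or a wrong sample size.

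The gain is about 0 to 2 points of power if baseline load is weakly prognostic (HR per SD up to 1.2), about 4 to 15 points if moderate (about 1.35 to 1.8), and more if strong, with essentially no loss if it is not prognostic. These figures assume exponential times, proportional hazards and a correctly specified linear index. The strength of that index cannot be read from the article.

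A reader might infer that adjustment brings the trial back to 80%. It does not do so in general. With the conditional HR fixed at 7/12, adjusted power stays between about 67% and 74%, close to the 73% seen with no covariate effect. The gap from 80% caused by the 29-day cap and discrete swab days is a separate matter.

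**What to change.** In Statistical methods {20a}, make the primary test and estimate the treatment term of a Cox model adjusted for baseline nasopharyngeal viral load, entered as a continuous variable. Specify the swab measurement, because the secondary outcomes list plasma viral load. Add entry clinical status (3, 4, 5) as a second prognostic factor whose benefit has not been quantified. Use Efron's method for ties, since patients share swab days. Fix the covariates before any outcome data are seen. Keep the unadjusted log-rank test, unadjusted hazard ratio and Kaplan-Meier curves as supportive.

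Amend {20c} at the same time. As written it leaves gaps unfilled, which would conflict with any rule for a missing baseline value. State that a missing baseline covariate, as distinct from a missing outcome, takes the overall mean plus a missing-value indicator, so that all randomised patients stay in the intention-to-treat analysis.

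The cost is wording in two sections, with no new patients, visits or assays. Because the stated primary analysis changes, it should be handled as a protocol amendment. The small downside is that the hazard ratio becomes conditional on baseline, so the unadjusted one should be reported beside it.

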#### Secondary outcomes

I)Improvement in clinical severity score, defined as percentage of patients reporting each severity rating on a 7-point ordinal scale (as defined above in the “Eligibility criteria {10}” section). [Time frame: baseline, days 7, 15, 21, and 29]. This study is underpowered to measure clinical efficacy. Nevertheless, measuring changes in the distribution of patients on the 7-point ordinal scale allows both to monitor the safety of the therapeutic regimen and detect potential positive changes in the clinical status of patients.Improvement in clinical severity score, defined as the time to clinical improvement of two points from the time of randomization on a 7-category ordinal scale or live discharge from the hospital, whichever comes first (as defined above in the “Eligibility criteria {10}” section). [Time frame: from baseline to day 29].Incidence of new oxygen use, non-invasive ventilation, or high flow oxygen devices during the trial. [Time frame: from baseline to day 29].Oxygenation free days in the first 28 days. [Time Frame: from baseline to day 29].Ventilator free days in the first 28 days. [Time frame: from baseline to day 29].Incidence of new mechanical ventilation use during the trial. [Time frame: from baseline to day 29].Number of patients transferred to Intensive Care Unit (ICU). [Time frame: from baseline to day 29].II) Mortality rate. [Time frame: from baseline to day 29].III) Changes from baseline in pulmonary CT imaging severity score measured with artificial intelligence and expressed as cc and percent values of diseased lung (lung consolidation, ground glass opacities and disease free) [Time frame: baseline, day 21; extra follow-up at 90 days].IV) Duration of hospital stay expressed in days. [Time frame: from baseline to day 29].V) Viral load measured on plasma with RT-PCR. [Time frame: baseline, days 3, 5, 7, 9, 11, 13, 15, 21, and 29].VI)Number of serious adverse events (SAE) and adverse drug reaction (expected and un-expected) until the discharge from the clinical unit (discharge for any motivation). [Time frame: from baseline to day 29]. This outcome addresses safety.Changes from baseline in white blood cell count (WBC), hemoglobin, platelets, C-reactive protein (CRP), lactate dehydrogenase (LDH), alanine aminotransferase (ALT), aspartate aminotransferase (AST), total bilirubin, creatinine, prothrombin time, international normalized ratio (INR), D-dimer, electrolytes (sodium, potassium, calcium), and glucose. [Time frame: baseline, days 7, 15, and 29]. IFNβ exerts broad-range effects on the immune system, being anemia, thrombocytopenia, and leukopenia reported as common events [21]. Thus, monitoring these markers, in conjunction with markers of inflammation, coagulation, and organ dysfunction, is of pivotal relevance to address safety.

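### Student's t test is named for continuous secondary and exploratory outcomes under 2:1 allocation; if the arms differ in SD its p-values are off the nominal 5%, and naming the Welch form would prevent this at almost no cost

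*Protocol article*

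**What the plan says.** The protocol article, section Statistical methods for primary and secondary outcomes {20a}, gives one rule for all continuous outcomes: Student's t "test or Mann-Whitney test (depending on the data distribution pattern) will be used for inter-group comparison of continuous variables". The section does not mention unequal variances or a Welch or Satterthwaite form. It sets the threshold in general terms ("Statistical significance will be determined at 5% significance level") and announces that "a detailed statistical analysis plan (SAP) will be written describing all analyses that will be performed".

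The Sample size {14} section fixes the imbalance: "120 total patients need to be randomized in 2:1 ratio", and after the allowance for drop-out, "84 patients in the IFNβ-1a arm and 42 in the standard of care arm".

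The rule reaches the continuous items under Secondary outcomes and Exploratory outcomes, for example change in CT severity, laboratory changes from baseline, plasma viral load, and oxygenation-free and ventilator-free days. The primary outcome, time to negative swab conversion, is analysed by Kaplan-Meier, log-rank and Cox methods, so it does not come under this rule.

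**The concern.** Student's t test estimates one common variance from both arms. With equal arm sizes a difference in SD does little harm, because the pooled standard error still has the right size on average. With arms of 84 and 42 it does not. The pooled variance is weighted towards the larger arm, while the true variance of the mean difference is driven more by the smaller arm. If the control arm is more variable, the pooled standard error is too small and the test rejects too often. If the IFNβ-1a arm is more variable, the standard error is too large and the test rejects too seldom.

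At stake is the calibration of the p-values for the continuous secondary and exploratory comparisons. The Discussion presents several of these as proxies for activity and efficacy.

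**Working it through.** **Inputs.** Arm sizes 84 and 42 come from Sample size {14}; they are consistent with its text (120 × 1.05 = 126; 126 × 2/3 = 84; 126 × 1/3 = 42). The 5% level comes from section {20a}. Two-sided testing is assumed, since two-sidedness is stated only for the hazard-ratio intervals. The protocol gives no SD, effect size or power for any continuous outcome, so there is no plan figure to reproduce. The SD ratios and the normal data below are assumptions.

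**Formulas.** With SDs s₁ (IFNβ-1a) and s₂ (control):

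- True variance of the mean difference: s₁²/84 + s₂²/42.
- What Student's test uses, on average: [(83 s₁² + 41 s₂²)/124] × (1/84 + 1/42).
- The square root of the second over the first is the factor by which the standard error is misjudged. Below 1 the test is too liberal, above 1 too conservative.

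**One case by hand, control SD 1.5 times larger (s₁ = 1, s₂ = 1.5).**

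- True variance: 1/84 + 2.25/42 = 0.0119 + 0.0536 = 0.0655.
- Pooled estimate: (83 + 41 × 2.25)/124 × 0.0357 = 1.413 × 0.0357 = 0.0505.
- Ratio of standard errors: √(0.0505/0.0655) = 0.878.
- The critical value 1.979 (124 degrees of freedom) therefore acts like 1.979 × 0.878 = 1.738. The two-sided tail beyond 1.738 is 8.2% under the normal distribution and 8.7% under t with the Satterthwaite 59.8 degrees of freedom.

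**All cases.** Levels are from 100,000 simulated trials per setting under no treatment difference.

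| Assumed SDs, IFNβ-1a : control | Pooled SE / true SE | True level, Student | True level, Welch |
|---|---|---|---|
| 2 : 1 | 1.23 | 1.7% | 4.9% |
| 1.5 : 1 | 1.14 | 2.6% | 5.0% |
| 1.25 : 1 | 1.08 | 3.5% | 4.9% |
| 1 : 1 | 1.00 | 5.0% | 5.0% |
| 1 : 1.25 | 0.93 | 6.8% | 4.9% |
| 1 : 1.5 | 0.88 | 8.7% | 5.1% |
| 1 : 2 | 0.82 | 11.3% | 5.0% |

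Repeat simulations with other random seeds gave 6.8% to 6.9%, 8.5% to 8.7% and 11.0% to 11.3% for the last three rows.

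**Cause.** With 63 patients per arm the ratio of standard errors is 1.00 throughout and Student's test stays at 4.9% to 5.1%. The 2:1 allocation is what makes unequal SDs matter.

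**Power.** For a mean difference that gives Welch about 80% power, Student's test has 76%, 72% and 66% when the IFNβ-1a SD is 1.25, 1.5 and 2 times larger. With equal SDs Welch gives up about 0.4 percentage points.

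**The named alternative.** Mann-Whitney at 84 and 42 rejects in about 3.2% of trials when the IFNβ-1a SD is twice the control SD and 8.1% in the reverse case (5,000 trials each). It is less distorted than Student's test at these ratios but shows the same pattern.

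**The case against.** The strongest reply is that the pooled form is inferred from the test's name. The protocol does not use the words pooled or equal variance, it announces a detailed SAP, and the variance form of a secondary-outcome t test is a detail that a SAP can settle. This limits the weight of the point but does not remove it. The protocol has already named a test, in its usual sense the equal-variance one, so the issue is a stated choice and not an omission. A SAP that names Welch would resolve it.

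A second reply is that many of these outcomes, such as D-dimer, viral load and ventilator-free days, are skewed and would go to Mann-Whitney. That is plausible and narrows the reach of the t test, although Mann-Whitney does not restore the nominal level when spreads differ. Whether the choice between the two tests should follow the observed distribution is a separate question, not argued here.

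A third reply is that moderate SD ratios do moderate harm: between 0.8 and 1.25 the level runs only from about 3.5% to 6.9%. This stands. The large errors need ratios near 0.5 or 2.

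A reader might also infer from the remark that IFNβ has "anemia, thrombocytopenia, and leukopenia reported as common events" that the treated arm will be more variable, so that the test errs in a predictable direction and a safety signal is likely to be missed. The protocol does not support this. The remark concerns how often such events occur, not spread, and a drug that lowers counts bounded below by zero could narrow the spread as well as widen it. Section {20a} says that safety data will be summarised by treatment group, and no safety decision is tied to a t-test p-value.

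**Conclusion.** The point holds as a minor one. With 84 and 42 patients, Student's t test has a true level of about 3.5% down to 1.7% if the IFNβ-1a SD is 1.25 to 2 times the control SD, and about 7% up to 11% if the control SD is larger by the same factors. Welch holds about 5% in all these cases. These figures rest on assumed SD ratios, normal data and two-sided testing. If the SDs are equal there is no error, and which way any error would run is unknown in advance.

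Two wider readings should be avoided. The first is that reported intervals or error bars for continuous outcomes would be wrong: the protocol specifies intervals only for hazard ratios ("presented together with 95% two-sided confidence intervals"). The second is that the trial's main conclusion is at risk: the log-rank and Cox analysis and the sample size built on it do not use this test.

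**What to change.** In section {20a}, and in the SAP, replace Student's t test with the Welch (Satterthwaite) unequal-variance t test wherever a t test is used. If a regression adjusted for the baseline value is used instead, specify heteroscedasticity-robust standard errors. The role of Mann-Whitney can stay as written for this purpose.

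The cost is one phrase, no additional data or patients, and about 0.4 percentage points of power if the SDs turn out equal. It should be settled before the final data are analysed.
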